### Study design and procedures

2.1

The study is a pilot randomized control trial with two parallel groups; a control group and an intervention group with a 1:1 allocation ratio. The study will only be blinded on pre-measurement. Afterward group assignment blinding is no longer possible because the pre-assessments and training sessions will be carried out by the same study staff. Data collection will be carried out in the neurologic rehabilitation clinic in Zihlschlacht, Switzerland. All study procedures will be performed in accordance with the Declaration of Helsinki. The study protocol was reviewed and approved by the Cantonal Ethics Committee of Eastern Switzerland (EKOS 24/002). Any substantial amendment to the study protocol will have to be approved by the same Ethics Committees and the trial registration at clinicaltrials.gov NCT06296069 will be updated accordingly.

At clinic admission, patients potentially fulfilling the eligibility criteria will be informed in oral and written form about the study and asked if they wish to participate. All interested participants will then be screened for eligibility by the local principal investigator. The included participants will undergo the baseline assessments (T1) and will be subsequently randomly allocated to the intervention or the control group using permuted block randomization with blocks of four. Screening and baseline measurements will be conducted within the first two days upon admission. To minimize physical and cognitive fatigue, a consistent assessment sequence alternating between physical and cognitive tests will be enforced. Participants will be encouraged to ask for a break whenever needed. One day after the T1 measurements, the intervention period will begin. The intervention period will be equal to the length of the stay in the rehabilitation clinic (between 3–4 weeks, according to cantonal/regional regulations and insurance coverage). At the last two days before discharge, post-measurements (T2-measurements) will be performed with all (intervention & control) study participants. Participants will be withdrawn from the study if they develop symptoms or diseases regarded as exclusion criteria during the study.

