### Participants and eligibility

2.2

Primary outcomes of this pilot study are feasibility measures (e.g., adherence, attrition, motivation, enjoyment, adverse events) which do not require an *a priori* sample size calculation. The selected sample size is based on the recommendations of Whitehead et al. (25). Since we are aiming for a future main trial designed with 90% power and two-sided 5% significance and aim to be able to detect medium effect sizes, we will use a sample size of n = 15 per treatment arm. Therefore, 30 participants will be included in the study with 15 participants allocated to each group (intervention or control group). Inclusion criteria are: prescription for inpatient rehabilitation due to a stroke, ability to provide a signed informed consent, age ≥ 50 years, Mini Mental State Examination (MMSE) ≥ 20, ability to stand for at least 3 min without external support. Exclusion criteria are: depending on assistance for ambulation (Functional Ambulation Categories <2), insufficient knowledge of the German language to understand the instructions and games, conservatively treated osteoporotic fractures in the last 16 weeks and presence of any mobility, cognitive, sensory and/or psychiatric limitations or comorbidities which impair the ability to play the exergames and/or conduct the pre-/post assessments.

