##### Attrition

2.4.1.2

The number of participants that dropped-out during the trial will be recorded for both groups. Drop-out reasons will be documented if available. Considering the median rate for attrition in preventive interventions for older adults in community settings for clinical trials (29) a 10% attrition rate can be deemed acceptable.

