#### Statistical analyses

2.4.4

All statistical procedures will be conducted with the IBM SPSS statistics software or R (RStudio, Boston, MA, United States). For demographics as well as training adherence and compliance, all collected data will be included (i.e., including data of dropouts up to the time point of their withdrawal). For all further analyses, only data of participants with an adherence ≥70% will be analyzed (per protocol analysis). A separate descriptive analysis of data from withdrawn participants who terminated the intervention prematurely or had to be excluded during the study or participants with adherence <70% will also be provided. Data will be reported as mean (SD) values for continuous parametric data and median (IQR) values for continuous nonparametric data. Data will be tested for normal distribution using Shapiro-Wilks Test and Q-Q-plots as well as for homogeneity of variance using Levene test. General level of significance used is established as *p* = 0.05. For the physical and cognitive tests that serve as secondary outcomes and are assessed in a pre-post manner, a two-way repeated measures ANOVA with group assignment (control vs. intervention group) as between subject factor and time-point (pre- vs. post-training) as within factor will be conducted. In case length of stay (and thus number of training sessions) vary across participants, we will conduct repeat our analyses controlling for this parameter. In order to determine the effects of the outcomes, effect sizes will be calculated for all primary and secondary outcomes. If any of the assumptions for parametric testing is not met, the non-parametric alternative (Friedman’s ANOVA) will be used. If the two-way mixed ANOVA or Friedman’s ANOVA report a significant group, time or interaction effect, data will be further analyzed using post-hoc tests. To calculate effect sizes of intragroup differences between post- and baseline measurements, a dependent T-test or its non-parametric equivalent (Wilcoxon signed rank test) will be used. The effect size will be interpreted using benchmarks describing the effect size as small (r ≥ 0.01), medium (r ≥ 0.3), or large (r ≥ 0.5) (56).

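### The cut-off for a small effect, r ≥ 0.01, does not belong on the same r scale as 0.3 and 0.5 and leaves almost no negligible category

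*Protocol article*

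**What the plan says.** The protocol article, section 2.4.4 (Statistical analyses), promises that "effect sizes will be calculated for all primary and secondary outcomes". For the size of change within each group it then says that "a dependent T-test or its non-parametric equivalent (Wilcoxon signed rank test) will be used". The next sentence gives the interpretation rule, with a literature reference (number 56), "describing the effect size as small (r ≥ 0.01), medium (r ≥ 0.3), or large (r ≥ 0.5". All three cut-offs carry the symbol r. No other section gives a different lower cut-off, names a variance-explained measure such as eta squared, or gives a reason for 0.01.

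The number behind each within-group comparison comes from section 2.2: "we will use a sample size of n = 15 per treatment arm". It can only fall from there. Section 2.4.1.2 says that "a 10% attrition rate can be deemed acceptable", and section 2.4.4 restricts the outcome analyses, so that "only data of participants with an adherence ≥70% will be analyzed (per protocol analysis".

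**The concern.** The values 0.3 and 0.5 are familiar benchmarks for a correlation-type effect size, and by general convention the set that contains them starts at 0.1. The value 0.01 is one tenth of that, and it is also exactly 0.1 squared. It could have arisen by losing a decimal place or by taking a variance-explained benchmark and labelling it r. On either account the three numbers do not form one scale.

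What is at stake is how results are described. This is a 30-person pilot with many cognitive and motor measures, and readers will look at the verbal labels. With the lower cut-off so close to zero, nearly every estimate gets a label of at least *small*, whether or not anything changed, and the labels stop separating a negligible result from a small one.

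**Working it through.** **Inputs.** Cut-offs 0.01, 0.3 and 0.5 (section 2.4.4); comparison value 0.1 (general convention, not in the document); n = 15 per arm (section 2.2); paired t-test or Wilcoxon signed rank test for the within-group comparison (section 2.4.4). The cut-off is a convention, so there is no figure of the plan's own to reproduce by calculation. The article does not give its formula for r; the usual conversions are assumed below.

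**Step 1: do the cut-offs share a scale?** Square each r, and convert it to a standardised difference for two equal groups by d = 2r/√(1 − r²).

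| r | r² | d |
|---|---|---|
| 0.01 (as written) | 0.0001 | 0.02 |
| 0.1 (convention) | 0.01 | 0.20 |
| 0.3 | 0.09 | 0.63 |
| 0.5 | 0.25 | 1.15 |

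As written, the step from *small* to *medium* is 0.3/0.01 = 30-fold, and the step from *medium* to *large* is 0.5/0.3 = 1.67-fold. With 0.1 the first step is 3-fold.

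**Step 2: what does the cut-off do when nothing has changed?** For a paired t-test, r = √(t²/(t² + df)) with df = n − 1. A cut-off c is therefore reached when |t| ≥ c·√(df/(1 − c²)). With n = 15 and df = 14:

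- c = 0.01: |t| ≥ 0.01 × √(14/0.9999) = 0.037, with two-sided null probability 97.1%.
- c = 0.1: |t| ≥ 0.1 × √(14/0.99) = 0.376, with null probability 71.3%.

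The labels given to null results at n = 15 are then:

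| Label | As written | With 0.1 |
|---|---|---|
| below *small* | 2.9% | 28.7% |
| *small* | 71.2% | 45.4% |
| *medium* | 21.0% | 21.0% |
| *large* | 4.9% | 4.9% |

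The share that changes label is 97.1 − 71.3 = 25.8%, about 26%. The *medium* and *large* rows do not move.

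**Step 3: does this depend on the test or on n?**

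- Exact Wilcoxon null distribution at n = 15, with r = |Z|/√N: 97.8% reach 0.01. For 0.1, 72.0% reach it with N = 15 pairs and 60.0% with N = 30 observations. The share relabelled is about 26% or 38%.
- Paired t at smaller n, to allow for drop-out and the adherence rule: at n = 13, 97.3% against 73.4% (24% relabelled); at n = 10, 97.7% against 77.0% (21% relabelled).
- If the labels were also used for a two-group contrast on 28 df: 95.8% against 59.9% (36% relabelled). The article does not say that r will be computed this way.

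**The case against.** The strongest reply is that little depends on this number, and most of that reply stands.

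- **Noise.** A reader might infer that the wrong figure is the reason why nearly all noise would be called an effect. It is only part of the reason. With the cut-off at 0.1, about 71% of null within-group results would still be called at least *small*, because 15 participants give imprecise estimates. The 97% also includes the 26% called *medium* or *large*, which the error does not touch.
- **Reach.** A reader might infer that the benchmark decides what the pilot concludes about the added value of the labile surface. The document does not support this. Feasibility is judged on three criteria listed at the end of section 2.4.1.8 (adverse events, attrition, adherence), none of which uses r. The comparison of labile with stable training is made by the group-by-time ANOVA at p = 0.05. The sample size of 15 per arm does not use the cut-off. The benchmark sentence follows directly on the within-group tests, so that is its clearest use; wider use is possible, given the promise of effect sizes for all outcomes, but it is not spelled out.
- **Cause.** A reader might take it as settled that a variance-explained value was mixed in. The cited source is not at hand, and a lost decimal place fits equally well.
- **Scenario.** No true change within a group is unlikely when both arms receive active inpatient rehabilitation early after stroke. That is fair. The null serves here only to show where the cut-off lies relative to chance variation; it does not predict this trial's results.

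None of this makes 0.01 fit beside 0.3 and 0.5.

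**Conclusion.** The stated lower benchmark is wrong as written. On the r scale shared by all three cut-offs, 0.01 corresponds to 0.01% of variance, against 9% and 25% for the other two, and nothing in the article explains it. At n = 15 per arm with no true pre-post change, it raises the share of within-group results called at least *small* from about 71% to about 97%, so about 26% of null results are moved out of the negligible range and only about 3% remain there. These figures assume that r is derived from a paired t-test in the usual way and that 0.1 is the intended companion of 0.3 and 0.5. The effect is confined to the verbal labels. Feasibility, sample size, significance level and hypothesis tests are unchanged. Severity: minor.

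**What to change.** In section 2.4.4, change the benchmarks to small r ≥ 0.1, medium r ≥ 0.3 and large r ≥ 0.5, and state that values below 0.1 are called negligible. If a variance-explained measure was intended, name it and restate all three cut-offs on that scale. The authors can settle which applies by checking their reference 56.

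The cost is one number and one sentence, with no change to design or data collection. The downside is that some results will be described less favourably.

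As optional good practice, separate from this error, a 95% confidence interval could be reported with each effect size, because even 0.1 lies well within chance variation at this sample size.

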## Results

3

Data collection is expected to start in February 2024 and to be completed in August 2024.

## Discussion

4

The goal of this pilot RCT is to evaluate the feasibility and effects of an exergame-based cognitive-motor training intervention on a labile surface in stroke inpatients. We expect the intervention to be feasible and more effective in improving motor and cognitive functioning compared to training on a stable surface.

Previous studies using the same exergame device in the same setting (inpatient rehabilitation) with geriatric and Parkinson’s inpatients reported no adverse events, very high adherence and enjoyment levels as well as significant time-group interaction effects for, e.g., gait speed, balance, psychomotor speed and inhibition (15, 16). However, exergame training on a labile surface has not been investigated neither for this population (stroke patients) nor in this setting (inpatient rehabilitation). Therefore, we extend previous intervention approaches by increasing proprioceptive stimulation during training and consequently training effects.

The main challenge we anticipate is low recruitment rate. Inpatient clinics (at least in Switzerland) offer a wide variety of therapies which are offered in a very intensive manner; patients can have up to 1.5 h of therapy per day. This can lead to participation in the study be seen as a burden. Moreover, the study population (persons in the early-subacute phase) is extremely heterogeneous which can affect interpretation of the effect results. What is more, the study will take place in an inpatient rehabilitation clinic and thus training volume will not correspond to the current training recommendations for stroke patients. After a systematic review, healthy elderly people should perform exergame training two to three times per week for 45–60 min for 12 weeks and more to improve cognition (57). In addition, this study’s results will not be generalizable to other stages of the disease (e.g., chronic stroke) or settings (e.g., outpatient rehabilitation). However, examining the feasibility of this intervention within the scope of this study will give valuable information about whether or not such training can be integrated in the inpatient rehabilitation therapy plans. In addition, if found effective, this study would be the foundation for a larger study that is powered to detect effects. Most importantly, the information and knowledge gained from this project will help to adapt and further develop digital solutions and technologies to support patients, therapists, geriatric rehabilitation and potentially the whole health care system.
